#### Aim 3(a):

We will fit a series of generalized estimating equations (GEE) models using the SAS® GENMOD procedure with each of the dichotomous adverse events, adherence (21+ sessions or  $\geq 90\%$ ) and satisfaction outcomes as the dependent variable; a binomial distribution for the outcome and a logit canonical link function; intervention arm, as the effect of primary interest; baseline value of outcome and any other measures found to be different between arms or deemed important as additional fixed effects covariates; and an exchangeable working correlation structure to account for clustering due to facility. We will appropriately construct contrasts to test hypotheses of differential proportions with adverse events based on intervention when delivered by exercise leaders.

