## **5 STUDY INTERVENTIONS**

### **5.1 Overview**

The exercise interventions will be delivered in 2 phases. The first phase or 12 week class will be delivered by the exercise leader. The second phase or 12 week class will begin once the first phase is completed and will be delivered by staff activity personnel. Participants who are randomized to the second phase class (i.e. delivered by staff activity personnel) will repeat the baseline testing prior starting the exercise class.

The facilities will be randomized (described above) to receive either the "On the Move" or a standard group exercise program. Both exercise programs (On the Move and standard) will be group-based and led by a person. Both programs will be delivered by trained exercise leaders or trained staff activity personnel (sustainability component). The frequency and duration of the programs are identical (50 minutes, 2 times a week for 12 weeks). From our past research we have determined that a frequency of 2 times per week for 12 weeks is acceptable to the older adult participants and is an adequate dose to obtain meaningful outcomes.(23) The main difference between the standard and the On the Move group exercise programs is the program content which is described below.

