### 5.6 Adherence Assessment

A roster of participants will be developed for each group exercise class. At the beginning of each class, attendance will be recorded by the exercise leader or staff activity personnel. Reasons for missed classes will be recorded when available. Attendance rate ([number of sessions attended

544 by the participant/total number of classes offered, i.e 24] X100%) will be calculated for each  
545 participant and will be the main indicator of adherence.

546

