##### Aim 3(b):

will fit a series of generalized estimating equations (GEE) models using the SAS® GENMOD procedure with each of the dichotomous adverse events, adherence (21+ sessions or  $\geq 90\%$ ) and satisfaction outcomes as the dependent variable; a binomial distribution for the outcome and a logit canonical link function; intervention arm, delivery model and their interaction as effects of interest; baseline value of outcome and any other measures found to be different between arms or deemed important as additional fixed effects covariates; and an exchangeable working correlation structure to account for clustering due to facility. We will appropriately construct contrasts to test hypotheses of differential proportions with adverse events based on intervention when delivered by staff activity personnel and delivery mode.

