#### 9.3.4 Additional

Exploratory/Sensitivity  
and  
Compliance/Dropout  
Analyses

**Figure 2.** Hypothetical template for summarization of Aim 4 results.

Figure 1. Predictors of treatment response using age, gait speed, and fear of falling. Area under ROC curve=0.797

[figure not shown]

We will perform additional analyses to extend our findings, generate new hypotheses, assess robustness and potentially refine conclusions. They will include using an alternative threshold besides 90% to operationally define high level of adherence/compliance calculating proportion missing each session to describe the pattern of adherence/compliance over time; assessing intervention effects using as-treated instead of intention-to-treat philosophy; and alternative operational definitions of treatment response such as combinations of walking ability, function and/or disability, and reaching a published threshold such as 0.4(0.8) m/s in gait speed for limited(full) community ambulation.(70)

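### The adherence cut-off of 21+ sessions or ≥90% does not agree with itself: with 24 classes, ≥90% needs 22 sessions, and 21 sessions is 87.5%

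*Supplement*

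**What the plan says.** All references are to protocol version 2.0.

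- **Section 9.3.2, Aim 3(a).** A GEE logistic model takes as one of its dependent variables "with each of the dichotomous adverse events, adherence (21+ sessions or" ≥90%).
- **Section 9.3.3, Aim 3(b).** The same definition is used again: "procedure with each of the dichotomous adverse events, adherence (21+ sessions or" ≥90%).
- **Section 5.6.** The attendance rate is the number of sessions attended "by the participant/total number of classes offered, i.e 24", expressed as a percentage. It is named as the main indicator of adherence.
- **Section 5.1.** The schedule agrees with 24 classes: "The frequency and duration of the programs are identical (50 minutes, 2 times a week for 12 weeks".
- **Section 9.3.4.** The additional analyses include "using an alternative threshold besides 90% to operationally define high level of adherence/compliance". Here 90% stands alone as the plan's cut-off.

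The protocol gives no rounding rule, no other denominator, and no statement of which half of the definition governs.

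**The concern.** The parenthesis reads as one threshold given in two units, a count and a percentage. With 24 classes the two are not the same threshold. Two analysts who follow the plan could code the same participant differently, and the choice between them could be made with the data in view.

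The outcome is used for a stated hypothesis. Section 1.2, Aim 3, expects higher attendance with On the Move than with the standard program, and similar attendance under the two delivery modes. The dichotomous adherence variable is modelled for both parts of that aim.

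**Working it through.** **Inputs.** Classes offered: 24 (section 5.6), which matches 2 per week × 12 weeks = 24 (section 5.1). Cut-offs: 21 or more sessions, and ≥90% (sections 9.3.2 and 9.3.3).

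**Do the two halves match?**
- 21 / 24 = 87.5%, below 90%.
- 0.90 × 24 = 21.6, so the smallest whole number of sessions that reaches 90% is 22.
- 22 / 24 = 91.7%.
- Rounding does not close the gap, because 87.5% rounds to 88%.

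Over every count from 0 to 24, the two rules disagree at exactly one value, 21.

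**Would another number of classes reconcile them?** With 23 offered, 21 / 23 = 91.3% and the two rules agree at every count. With 22 offered, ≥90% needs 20 sessions (0.90 × 22 = 19.8), so they disagree at 20. Only 23 works among 20 to 24, and the protocol says 24.

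**How many participants could sit at exactly 21?** The documents give no expected attendance, so this part rests on assumptions. Suppose every participant attends each class independently with the same probability p. Then P(exactly 21) = C(24, 21) × p^21 × (1 − p)^3.

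| Assumed p | Exactly 21 | Adherent at 21+ | Adherent at 22+ |
|---|---|---|---|
| 0.70 | 3.1% | 4.2% | 1.2% |
| 0.75 | 7.5% | 11.5% | 4.0% |
| 0.80 | 14.9% | 26.4% | 11.5% |
| 0.85 | 22.5% | 50.5% | 28.0% |
| 0.90 | 22.1% | 78.6% | 56.4% |

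**Allowing attendance to differ between people.** Equal and independent attendance is a strong assumption. Section 8.1 itself anticipates runs of missed classes through illness, injury, vacation or caregiving. A beta-binomial model with an assumed within-person correlation of 0.1 to 0.3 gives these shares at exactly 21:

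| Assumed mean attendance | Exactly 21, beta-binomial | Exactly 21, binomial |
|---|---|---|
| 0.70 | 7% to 8% | 3% |
| 0.80 | 7% to 12% | 15% |
| 0.85 | 6% to 12% | 22% |
| 0.90 | 5% to 11% | 22% |

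Variation between people therefore lowers the figure at high attendance and raises it at low attendance. Over all the assumptions tried, the share runs from about 3% to 22%.

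**The case against.** The strongest reply is that the rule can be applied as written. If the word joining the two halves is a logical union, a participant is adherent on meeting either one. With 24 classes everyone at ≥90% already has 21 or more, so 21+ decides every case. That reading is possible, but it leaves the percentage with nothing to do and puts the working cut-off at 87.5%. Section 9.3.4 would then misdescribe it as 90%. The percentage might have been meant for classes with fewer sessions held, but section 5.6 gives the denominator as 24 and says nothing of that kind. The sections need reconciling on either reading.

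A second reply is that 21+ may be what was intended, with 90% as a loose rounding. The documents do not exclude this. Section 9.3.4 favours 90%, but the count is written twice, so the choice belongs to the sponsor.

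A third reply concerns weight, and it stands. Aim 3 is a secondary objective worded as exploration. The attendance rate itself, which is not affected, is the main indicator of adherence. Section 9.3.4 already plans another threshold, so sensitivity to the cut-off would be examined, although that does not settle which cut-off is the main one.

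A reader might infer more than this from the table: that a fifth or more of participants would be misclassified, or that the comparison of adherence between programs is biased. The documents support neither. The 22% depends on a chosen attendance level and on equal, independent attendance. One cut-off would apply to both arms, so a change in the overall adherent share is not in itself a change in the contrast between arms.

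**Conclusion.** The definition is wrong as written. With 24 classes, 21+ sessions and ≥90% are different thresholds, and participants with exactly 21 sessions are classified differently by them. That follows from the protocol's own figures and needs no assumption.

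The number affected does need assumptions, and about 3% to 22% of participants is a fair range. The upper end requires high attendance that is equal and independent across participants.

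The consequence is confined to the dichotomous adherence outcome in Aims 3(a) and 3(b). The Aim 1 analysis, the sample size and the power do not depend on it, and no effect on the between-arm contrast has been shown. It is a small point, but worth correcting before the data are analysed, because the outcome serves a stated hypothesis and the definition leaves a choice open.

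**What to change.** Before analysis, state one cut-off in sections 9.3.2 and 9.3.3 that agrees with section 9.3.4.

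- The change that fits section 9.3.4 is **22+ sessions (≥90%)** in both places, with 21+ (87.5%) kept as one of the alternative thresholds already planned.
- If the sponsor intended 21+, restate the percentage as **≥87.5%** in sections 9.3.2, 9.3.3 and 9.3.4.
- In the same edit, say which denominator applies if a class series holds fewer than 24 sessions, since the count and the percentage then separate in a different way.

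The first option changes one figure in two sentences, and the second changes the percentage in three sections. No data collection changes. The downside of 22+ is that the adherent proportion falls by the share of participants at exactly 21 sessions, which may not be small: under the independent model at 0.85 per class, from 50.5% to 28.0%.

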### **1.2 Secondary Objectives**

**Aim 2: When feasible to be delivered by staff activity personnel, explore the effectiveness of *On the Move* compared to a standard program; and sustainability compared to delivery by exercise leaders (when feasible). Explore barriers to identifying and training staff activity personnel.** *On the Move delivered by staff activity personnel (when feasible) will produce gains in above outcomes that are greater than the standard program; and comparable to when delivered by an exercise leader.*

**Aim 3: Explore the acceptability and the risks of the *On the Move* and standard exercise programs delivered by (a) exercise leaders and (b) staff activity personnel (when feasible).** *On the Move will result in greater satisfaction and higher attendance rates than the standard program. Attendance rates and satisfaction will be similar for exercise leader and staff activity personnel led programs when feasible to recruit staff personnel. Adverse event (falls, soft tissue injuries, muscle soreness, etc.) rates during exercise will be similar between the two groups and the two facilitators when feasible to recruit staff personnel.*

**Aim 4: Explore potential baseline predictors of benefit and risks of participation in *On the Move* program to facilitate informed patient decision making.** *We will be able to identify combinations of baseline physical, psychosocial and demographic factors associated with each of the treatment response and adverse events outcomes.*

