| SPPB                                                |               | X                              | X                                                      | X                                |
| Figure 8                                            |               | X                              | X                                                      | X                                |
| GES                                                 |               | X                              | X                                                      | X                                |
| Physical Function                                   |               |                                |                                                        |                                  |
| LLFDI                                               |               | X                              | X                                                      | X                                |
| Global items                                        |               | X                              | X                                                      | X                                |
| Potential confounders                               |               |                                |                                                        |                                  |
| PHQ-9                                               |               | X                              | X                                                      | X                                |
| Digit Symbol Substitution Test                      |               | X                              | X                                                      | X                                |
| Program Evaluation                                  |               |                                |                                                        |                                  |
| Satisfaction survey                                 |               |                                |                                                        | X                                |

550  
551  
552

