Satisfaction will also be assessed by surveys in all participants at the conclusion of the exercise program. The satisfaction survey includes five items measured on a Likert scale and three yes/no questions. The Likert items will assess degree of satisfaction with various components of the exercise program (i.e. the exercises, instructor, music, space, and the overall program). We will also use a series of yes/no questions to determine if the program has meet the participants' expectations, if they feel they have benefited from the program, and if they would recommend the program to others.

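### The Aim 3 models adjust for a baseline value that adherence, satisfaction and exercise-related adverse events do not have; without it, no covariate is prespecified

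*Supplement*

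**What the plan says.** All references are to protocol Version 2.0 in the Supplement.

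Section 9.3.2, Aim 3(a), plans a series of binomial GEE models with a logit link and exchangeable correlation within facility. The dependent variables are the dichotomised adverse events, adherence and satisfaction outcomes. Arm is the effect of interest, and the covariates are "baseline value of outcome and any other measures found to be different between arms or deemed important as additional fixed effects covariates". Section 9.3.3, Aim 3(b), uses the same rule with delivery mode added: "intervention arm, delivery model and their interaction as effects of interest; baseline value of outcome and any other measures found to be different between arms".

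The measurement sections say when these outcomes come into being:

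- **Satisfaction** (6.2.3): "Satisfaction will also be assessed by surveys in all participants at the conclusion of the exercise program". On content: "The Likert items will assess degree of satisfaction with various components of the exercise program". In the section 6.1 schedule the row "Satisfaction survey" is marked only at the 12-week post-intervention visit.
- **Adherence** (5.6): "At the beginning of each class, attendance will be recorded by the exercise leader or staff activity personnel". The rate is sessions attended out of 24.
- **Adverse events** (1.2, Aim 3): "Adverse event (falls, soft tissue injuries, muscle soreness, etc.) rates during exercise will be similar between the two groups". Section 7.6 captures expected events by interview at 12, 24 and 36 weeks and lists no baseline interview.

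Fall history is scheduled at Baseline 1, Baseline 2 and 12 weeks (6.1). Section 9.1 stratifies the randomisation of facilities by facility type.

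**The concern.** Adjusting for the baseline value suits the continuous change scores of Aims 1 and 2, where the same instrument is used before and after the programme. The Aim 3(a) and 3(b) clause matches the one in the Aim 2 model, and it does not fit outcomes that exist only once the classes run.

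What is at stake is the adjustment set. The baseline value is the only covariate these models name. If it is void, the rest is an open clause: some covariates enter because the arms turn out to differ on them, others because someone judges them important. In a logit model the arm odds ratio depends on which covariates are included, even when they are balanced, so an open list also leaves open which odds ratio is being estimated. These models carry the trial's formal between-arm safety contrasts.

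**Working it through.** The plan gives no figure to reproduce here; the check is mainly a comparison of sections.

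**Step 1. Does each outcome have a pre-programme value?**

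| Outcome family | When it arises | Value before the programme |
|---|---|---|
| Satisfaction | End of programme (6.1, 6.2.3) | None; the items rate the programme itself |
| Adherence | Each of 24 classes (5.6) | None |
| Adverse events | During exercise (1.2); interviews at 12, 24 and 36 weeks (7.6) | None as defined; fall history (6.1) is an analogue for falls only |

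So 0 of 3 outcome families has a scheduled baseline value.

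**Step 2. What does the void term do to the model?** If it is set to a constant for everyone (for example, no event before the programme), it is collinear with the intercept. This was checked on illustrative simulated data, with assumed inputs: 28 facilities of 10 people, a facility effect with SD 0.5 on the log-odds scale, fall history in 25% of people, and an intercept log-odds of −2.

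- Intercept, arm and constant baseline value: 3 columns, rank 2. The term is not estimable.
- Intercept and arm: 2 columns, rank 2. The GEE converges.
- Intercept, arm and binary fall history: 3 columns, rank 3. The GEE converges.

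The fault is confined to the one term.

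**Step 3. What adjustment is left?** Compare the sections:

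- Aim 1 (9.3.2): the baseline value is the named covariate. Measures that differ between arms or are judged important are considered only to assess robustness.
- Aims 3(a) and 3(b): the baseline value is void, and the same data-chosen measures sit in the main model.
- Facility type, the stratification factor in 9.1, is named in neither Aim 3 model.

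Once the void term goes, Aim 3 has no prespecified covariate.

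**Step 4. Could fall history replace it for falls?** Section 7.1 expects major risks such as a cardiac event or a fall in under 1% of people. Taking that as the rate of people with a fall during the programme (an assumption):

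- Aim 1 sample: 0.01 × 280 = 2.8, so at most 2 people. Arm by fall history gives 4 cells, so at least 4 − 2 = 2 cells have no event.
- Full sample: 0.01 × 400 = 4, so under 4, at most 3 people. The four arm-by-delivery-mode groups in Aim 3(b) then include at least 4 − 3 = 1 with no fall. The interaction model is already in difficulty before fall history is added.

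The convergence in step 2 gives no reassurance at this rate. Its intercept implies an event probability of 1/(1 + e²) ≈ 0.12 in the reference group, far above 1%.

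**The case against.** The strongest reply is that this is a wording slip. An analyst would omit a covariate that does not exist, and step 2 shows that the arm contrast remains estimable. Aim 3 is worded as exploratory in section 1.2, and Aim 3(b) sits under exploratory analyses in 9.3.3. The open clause is arguably a separate weakness that would exist even if the baseline term were valid. Much of this stands and keeps the point modest. It does not answer step 3: omitting the void term is what leaves the open clause as the entire adjustment set. Aim 3(a) also sits under the main analysis heading of 9.3.2.

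Three stronger readings are tempting, and the documents do not support them.

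- **That the Aim 3 models cannot be fitted.** This is true only of the literal specification.
- **That fall history is ignored, or is the one useful baseline measure.** The plan does not name it, but the clause for measures judged important permits it, and for falls it could be read as the baseline value. Comorbidities, gait speed, SPPB and PHQ-9, among others, are also collected at baseline, and the plan does not rank them.
- **That Aim 3(b) would lose all leader-led participants, 280/400 = 70%.** This would require treating adverse-event interviews from the second-phase group's waiting period as a baseline value. No section says so. Section 1.2 confines the events to exercise, and the parallel Aim 2 model takes the first baseline for its main analysis and Baseline 2 only for sensitivity. Section 9.3.1 also plans multiple imputation rather than deletion, although imputing a value that never existed would mean nothing.

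**Conclusion.** The point holds as a specification error of limited consequence. The baseline-value covariate is undefined for adherence, satisfaction and adverse events during exercise in both Aim 3(a) and Aim 3(b). Removing it costs nothing in estimability, but leaves every Aim 3 model without a prespecified covariate and without the stratification factor. Use of fall history in the falls model is not prespecified.

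No change in type I error, power or sample size is shown, and Aim 1 is untouched. The conclusion rests on the definition of adverse events as occurring during exercise and on the section 6.1 schedule being complete. The caution about falls rests on the rate in section 7.1; if falls prove more frequent, adjustment for fall history becomes easier to support.

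**What to change.** In the Aim 3(a) paragraph of 9.3.2 and the Aim 3(b) paragraph of 9.3.3:

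1. Delete the baseline value of the outcome from the covariates.
2. Name facility type, with the levels used in the randomisation, as the prespecified covariate in the primary Aim 3 models.
3. Move measures that differ between arms or are judged important to a robustness analysis, as 9.3.2 already does for Aim 1.
4. For falls, name Baseline 1 fall history as a covariate in both delivery modes if the number of events supports it. State the minimum event count in advance, and say how the falls model is simplified below it. At the expected rate, even facility type may be too much for that outcome.

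Add a clause to section 9.3.1, whose general rule puts significant baseline differences into the main analyses and would otherwise conflict with item 3.

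The cost is about one sentence in each of the two Aim 3 paragraphs and the clause in 9.3.1. Facility type is known from the randomisation and fall history is already scheduled, so no new data are needed.

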## **7 SAFETY ASSESSMENTS**

### **7.1 Expected Adverse Experiences**

1. Major risks such as a cardiac event or a fall are expected to be rare – expected to occur in less than 1% of people (less than 1 out of 100 people).(55) Gardner et al, 2000,(55) reviewed controlled clinical trials of exercise interventions for older adults at-risk for falling. No cardiac events or falls were reported in the 12 clinical trials reviewed. The at-risk older adults in the studies reviewed have slightly poorer physical performance than the older persons we expect to recruit for our study. In our recent MOBILE study, a 1 year cohort study of 120 older adults participating in 3 clinic visits over a 1 year period there were no cardiac events or falls reported. In all conditions of testing in which the

participant is standing and/or walking (eg conditions with a potential risk for falling), the participant will be directly supervised by the trained tester. The trained tester is present for all testing sessions. We expect this level of supervision reduces the risk of falling to an even greater degree.

2. Less severe risks of participation such as muscle soreness, fatigue, or minor sprains or strains with each assessment, are expected to be infrequent – expected to occur in 1-10% of people (1-10 out of 100 people). Gardner et al, 2000,(55) reviewed controlled clinical trials of exercise interventions for older adults at-risk for falling, finding reports of such side effects of the intervention reported in only 4 of the 12 studies reviewed. The side effects were not a reason for dropout from the study and were described as soreness or musculoskeletal symptoms, but no injuries.
3. There is a rare risk that confidentiality could be breached. All of the research records will be kept in a locked file cabinet and/or password protected files. All of the investigators and staff that assist with the management of the files are trained in the privacy and confidentiality regulations that govern research.

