### 9.2 Sample Size

We base our sample size justification on prior data from our RESTORE and PRIME pilot studies, two-tailed tests conducted at the  $\alpha=0.05$  level, a conservative attrition rate of 10% between baseline and follow-up assessments, practical consideration of a class size of 10 participants for group exercise, computational techniques that match our study design and proposed analytical approach as much as possible within the constraints of already published methodologies and commercially available sample size and power software (PASS 2002®, Number Cruncher Statistical Systems, Inc., Kayesville, Utah), and ability to detect differences that correspond to published meaningful change criteria(57) or moderate Cohen's effect sizes of  $d=0.5$ .(58)

The numbers needed to enroll in order to detect statistical significance of intervention effect when delivered by an exercise leader (Aim 1), are presented in **Table 1**. We take into account the clustering of participants by facility by assuming an intracluster correlation of 0.1 and a resulting design effect of 1.90 to appropriately inflate the sample size accordingly.(59) In

summary, a total of 280 participants with 140 in each arm will allow us to detect statistical significance in intervention effects in all main outcomes with at least 80% statistical power.

**Table 1. Number needed to enroll for detecting effects of intervention incorporating clustered design (x1.90), attrition (10%), and rounded up to class size of 10.**

| Outcome                    | Prior Information                |                                 |                                         | Estimated Sample Size                                   |                                 |
|----------------------------|----------------------------------|---------------------------------|-----------------------------------------|---------------------------------------------------------|---------------------------------|
|                            | Baseline Standard Deviation (SD) | SD in Baseline-Follow up Change | Meaningful Difference Targeted (Source) | Completers Needed Per Arm assuming No Clustering | Number Needed to Enroll Per Arm |
| LLFDI Overall Function     | 6.15                             | 4.86                            | 3.08 ( $d=0.5$ )                        | 41                                                      | 90                              |

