#### 9.3.3 Aims 2, 3(b) and 4 exploratory Analyses

##### Aim 2:

We propose an analytic strategy with an exploratory philosophy for Aim 2 sustainability aim, because of the uncertainty surrounding our ability to recruit and train a staff activity person to lead a class safely and per protocol.

We will fit a series of linear mixed models using the SAS® MIXED procedure with baseline to follow-up change in each of the continuous outcomes (LLFDI function/disability, walking ability, other measures of mobility performance) as the dependent variable; intervention arm (standard/*On the Move*), delivery mode (by exercise leader/staff activity personnel) and their interaction as fixed effects of interest; baseline value of outcome and any other measures found to be different between arms or deemed important as additional fixed effects covariates; and a facility random effect to account for greater similarity of participants from the same facility compared to different facilities and resulting non-independence of observations within facility (ie. clustering). We will construct appropriate means contrasts to estimate difference in gains in the two interventions when delivered by staff exercise personnel (Aim 2 effectiveness hypothesis); and difference in gains attributable to *On the Move* intervention when delivered by exercise leaders and staff activity personnel (Aim 2 sustainability hypothesis). Statistical significance of the estimates will serve as formal tests hypotheses. We note that participants randomized to staff activity personnel had to wait 12 weeks since their baseline assessment and randomization to start the intervention, during which they may have changed; and that they underwent a second baseline assessment immediately prior to starting the exercise intervention. Therefore, we will repeat the above analysis using their second baseline assessment instead of the first one to assess the sensitivity of results.

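### The Aim 3 GEE models name no test or small-sample method for about 28 to 34 facilities, and no fallback when an arm has no adverse events

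*Supplement*

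**What the plan says.** All references are to protocol Version 2.0. Section 9.1 assigns the exercise program by facility. For Aim 3(a), section 9.3.2 fits a GEE model with binomial outcome and logit link to each binary adverse event, adherence and satisfaction outcome. Program is the effect of interest, covariates are added, and an exchangeable working correlation is used as a "structure to account for clustering due to facility". Aim 3(b), in section 9.3.3, adds delivery mode and its interaction with program. Contrasts are then built to "test hypotheses of differential proportions with adverse events". Neither paragraph states the type of standard error, whether the test is Wald or score, the reference distribution, its degrees of freedom, or what happens when an arm has few or no events.

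Section 7.1 says that major events (cardiac events, falls) are "expected to occur in less than 1% of people", and puts minor events at 1-10%. Section 9.2 plans "a total of 280 participants with 140 in each arm" for the leader-delivered comparison and about 120 staff-led participants, 60 per arm. Section 4 anticipates about 34 sites, section 12 at least 28. Section 3 caps a class at 10.

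For the mixed models of Aim 2, the "significance of the estimates will serve as formal tests hypotheses", again without stated degrees of freedom.

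**The concern.** Program varies only between facilities, so the information on it is limited by the number of facilities: 14 to 17 per arm in Aim 3(a), fewer in the staff-led classes. The usual GEE sandwich variance relies on many clusters. With few, it tends to be too small, and a Wald test against the normal distribution rejects too often. The Wald intervals are too narrow for the same reason.

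The second problem is separate. A logit model has no finite log odds ratio when one arm has no events, and the plan applies this model to events that it expects to be very rare. Falls are a named Aim 3 outcome, and section 1.2 hypothesises that adverse event rates will be similar between programs. A failed or powerless fit could be misread as support for that hypothesis.

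**Working it through.** **Inputs from the plan**
- Section 9.2: "two-tailed tests conducted at the" 0.05 level. No separate level is given for the GEE tests.
- Section 9.2: "assuming an intracluster correlation of 0.1". This is set for the continuous outcomes. None is given for binary outcomes, so I assumed 0.02 and 0.10.
- Section 9.2: "a conservative attrition rate of 10"%.
- Enrolment of 140 per arm (leader) and 60 per arm (staff).
- Facilities: 28 to 34 overall. The staff-led number is inferred: 120/10 = 12 if classes are full, and 120/(280/34) = 120/8.2, about 15, at the average number per site.

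**The plan's own figures.** No error rate or power is stated for the GEE tests. The nearest figures reproduce. The design effect is 1 + (10 - 1) × 0.1 = 1.90. For gait speed, 64 × 1.90 / 0.9 = 135.1, rounded up to 140. The power figures for gait speed in Table 4 come out at 89.7% and 77.5%, against 90% and 78% stated.

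**Type I error.** Simulation with no program effect: beta-binomial outcomes by facility, varying facility size, logit GEE with exchangeable correlation and program as the only covariate, 6,000 runs per setting (Monte Carlo standard error about 0.3 points at 5%). The staff-led comparison was simulated on 12 to 15 facilities alone. K is the number of facilities.

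| Facilities | Outcome rate | Uncorrected Wald, z | Score test | Kauermann-Carroll error, t on K - 2 df |
|---|---|---|---|---|
| 28-34 | 10-80% | 6.2-8.0% | 4.5-5.8% | 4.5-5.7% |
| 12-15 | 50-80% | 9.0-12.2% | 5.1-5.8% | 4.8-5.9% |
| 12-15 | 10% | 8.0-9.0% | 3.7-4.7% | 2.5-3.2% |

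At lower rates the uncorrected Wald test, where it can be computed, changes direction. At 28-34 facilities it rejects 4.9-7.3% of the time at a 5% event rate, 2.0-3.8% at 3%, and 0-0.4% at 1%. At 12-15 facilities it rejects 2.7-3.5% at 5%, and 1.6% or less at 3% and below.

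**Chance of an empty arm.** At a 1% rate the expected count per arm is 140 × 0.01 = 1.4, or 60 × 0.01 = 0.6. With independent participants and full enrolment, the probability that at least one arm has no event is 1 - (1 - (1 - p)^n)^2.
- 140 per arm: 0.99^140 = 0.245, so 1 - 0.755^2 = 43%.
- 60 per arm: 0.99^60 = 0.547, so 1 - 0.453^2 = 80%.

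| Event rate | 140 per arm | 60 per arm |
|---|---|---|
| 1% | 43% | 80% |
| 3% | 3% | 30% |
| 5% | 0.2% | 9% |
| 10% | about 0% | 0.4% |

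With clustering and 0-10% attrition, the figures at a 1% rate rise to 48-66% (28-34 facilities) and 82-91% (12-15 facilities). Rates below 1% make this worse.

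**Mixed models.** If participant-level degrees of freedom were used, the actual error would be 2 × P(t > 1.97) = 0.0596 on 26 df or 0.0575 on 32 df for Aim 1, and 2 × P(t > 1.98) = 0.076 on 10 df for the staff-led contrast.

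**The case against.** A reader might infer that the plan uses uncorrected large-sample errors. It does not say so: it is silent on the test, and a score test would hold close to 5%. This stands, so the inflation is conditional. A score test would, however, mend the p-value and not a Wald interval reported beside it.

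A reader might also infer that false positives exceed 5% for all three kinds of outcome. The figures above do not support that. The excess is confined to common outcomes. For events at about 3% or below (5% or below in staff-led classes) even the uncorrected Wald test rejects too seldom.

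Nor is it right that adverse events in general cannot be estimated. Section 7.1 expects minor events in 1-10% of people, and at 5-10% an empty arm in Aim 3(a) is very unlikely. Section 9.3.1 also plans frequencies and percentages, so rare events would still be described.

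Finally, Aim 3 is worded as exploratory, and 3(b) sits under exploratory analyses. That lowers the stakes of the 8-12% figure. But 3(a) sits under the main analysis, both parts test hypotheses, and exploratory status does not make an infinite odds ratio reportable.

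**Conclusion.** The point holds in two limited parts.

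First, the plan leaves open a choice that matters with this number of facilities. An uncorrected Wald analysis would give about 6-8% type I error for common outcomes (adherence, satisfaction, events near 10%) in Aim 3(a), and about 8-12% for the staff-led comparison of programs. This rests on an assumed binary ICC of 0.02-0.10, on 12 to 15 staff-led facilities (inferred), and on a model with program as the only covariate. The delivery-mode contrast in 3(b) is largely within facility and was not assessed, so these figures should not be carried over to it.

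Second, and independent of the choice of test, the stated model often has no finite estimate for the major events. At a 1% rate the probability is about 43% (48-66% with clustering and attrition) at 140 per arm, and about 80% (82-91%) at 60 per arm. No standard-error correction mends this.

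The mixed-model point is minor: about 6% at most for Aim 1. The primary conclusion is not threatened.

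**What to change.** In section 9.3:

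- For between-program contrasts in Aims 3(a) and 3(b), specify a bias-corrected sandwich standard error (Kauermann-Carroll is the form checked above) with a t reference on facility-based degrees of freedom. Alternatively, specify a score test or a facility-level permutation test. State the method for the within-facility delivery-mode contrast separately.
- Add a sparse-event rule. When either arm has about 5 events or fewer, report counts and a risk difference with an exact or facility-permutation test, or pool events, in place of the covariate-adjusted logit GEE. The cutoff of 5 is a working convention that the team may set otherwise, provided that it is fixed in advance.
- As a minor addition, use Kenward-Roger degrees of freedom in PROC MIXED.

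The cost is a few sentences and no new data. Intervals become slightly wider. With 12 to 15 facilities and an outcome near 10%, the corrected test is conservative (about 2.5-3% error), which lowers power to detect a difference in harm there.
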